# Co-creation using crowdsourcing to promote PrEP adherence in China: study protocol for a stepped-wedge randomized controlled trial

**DOI:** 10.1186/s12889-022-14117-5

**Published:** 2022-09-07

**Keywords:** Co-creation, PrEP, Adherence, China, GBMSM, Transgender, Stepped-wedge design, Randomized controlled trial

## Abstract

**Background:**

Adherent pre-exposure prophylaxis (PrEP) uptake can prevent HIV infections. Despite the high HIV incidence, Chinese key populations have low PrEP uptake and adherence. New interventions are needed to increase PrEP adherence among key populations in China. Co-creation methods are helpful to solicit ideas from the community to solve public health problems. The study protocol aims to describe the design of a stepped-wedge trial and to evaluate the efficacy of co-created interventions to facilitate PrEP adherence among key populations in China.

**Methods:**

The study will develop intervention packages to facilitate PrEP adherence among Chinese key populations using co-creation methods. The study will then evaluate the efficacy of the co-created intervention packages using a stepped-wedge randomized controlled trial. This four-phased closed cohort stepped-wedge design will have four clusters. Each cluster will start intervention at three-month intervals. Seven hundred participants who initiated PrEP will be recruited. Participants will be randomized to the clusters using block randomization. The intervention condition includes receiving co-created interventions in addition to standard of care. The control condition is the standard of care that includes routine clinical assessment every 3 months. All participants will also receive an online follow-up survey every 3 months to record medication adherence and will be encouraged to use a WeChat mini-app for sexual and mental health education throughout the study. The primary outcomes are PrEP adherence and retention in PrEP care throughout the study period. We will examine a hypothesis that a co-created intervention can facilitate PrEP adherence. Generalized linear mixed models will be used for the primary outcome analysis.

**Discussion:**

Developing PrEP adherence interventions in China faces barriers including suboptimal PrEP uptake among key populations, the lack of effective PrEP service delivery models, and insufficient community engagement in PrEP initiatives. Our study design addresses these obstacles by using co-creation to generate social media-based intervention materials and embedding the study design in the local healthcare system. The study outcomes may have implications for policy and intervention practices among CBOs and the medical system to facilitate PrEP adherence among key populations.

**Trial registration:**

The study is registered in Clinical Trial databases in China (ChiCTR2100048981, July 19, 2021) and the US (NCT04754139, February 11, 2021).

**Supplementary Information:**

The online version contains supplementary material available at 10.1186/s12889-022-14117-5.

## Background

Despite many control programs, HIV incidence is still high among key populations in China. The national prevalence of HIV from 2001 to 2018 among gay, bisexual and other men who have sex with men (GBMSM) was estimated to be 5.7% (95% CI: 5.4–6.1%) [1]. Sexual transmission has become the preeminent route for HIV infection since 2014, with 95% of cases reportedly due to sexual transmission [2, 3]. The proportion of HIV cases due to heterosexual contact increased from 50% in 2010 to over 70% in 2018 [4]. HIV prevalence among Chinese MSM rose from 1.5% in 2005 to 7.0% in 2018 [4, 5]. The evolving patterns of HIV infections in China require new interventions.

Pre-exposure prophylaxis (PrEP) is highly effective in preventing new HIV infections among adherent key populations [6–8]. However, suboptimal adherence to PrEP in real-world studies is a substantial barrier [9, 10]. In China, TDF-FTC was only approved in August 2020 for PrEP. PrEP access is limited to urban infectious disease hospitals and not covered by national health programs or major health insurance plans. As a result, PrEP awareness and uptake are still low among Chinese key populations [11, 12], and data on PrEP adherence is scarce. Using self-reported adherence to daily PrEP, a study among 584 MSM in western China suggested a median adherence rate of 64.3% in 2018 [13]. The low engagement in the PrEP care continuum among key populations calls for innovative efforts to promote PrEP use. In particular, as PrEP moves into routine HIV prevention care practice and China is taking steps to scale up PrEP uptake, optimizing medication adherence becomes increasingly critical to fully realize its potential. Prior interventions have used mobile phone applications, text messages, and incentives to increase PrEP adherence among key populations in global settings [14–17]. However, these interventions were not tailored to the focus community or were based on sociocultural settings that were less suitable for key populations in China.

Crowdsourcing is a method of co-creation that uses a bottom-up approach to solicit ideas from groups of people to solve all or part of a practical problem [18, 19]. Crowdsourcing has been increasingly implemented to develop public health interventions [20]. Data from our previous study suggested that video campaigns generated through crowdsourcing can effectively strengthen and expand community-based HIV testing services for Chinese MSM [21]. Compared to conventional approaches, crowdsourcing may facilitate community engagement, while creating novel solutions to public health problems that resonate with the community [22]. In particular, crowdsourcing can help engage vulnerable groups who are often excluded from research projects [23]. However, most crowdsourced interventions in sexual health research centered on HIV testing services and promoting sexual health programs [24]. Preliminary data from pilot programs suggest that crowdsourcing methods could be used to promote PrEP uptake [24].

The study proposal aims to describe the design of a stepped-wedge trial and to evaluate the efficacy of a crowdsourced intervention to facilitate PrEP adherence among at-risk populations in China.

## Trial aims

Our study will use a crowdsourcing open call to develop a PrEP adherence intervention that will be implemented and evaluated using a stepped-wedge cluster randomized trial. The aim of this stepped-wedge trial is to improve PrEP adherence through crowdsourced intervention. We hypothesize that a crowdsourced intervention can facilitate PrEP adherence.

## Methods/design

### Study design and rationale

This pragmatic stepped-wedge cluster randomized trial is a sub-study of a multi-center demonstration of PrEP engagement and initiation among at-risk populations in two Chinese provinces, Hubei and Guangdong. (Study ID: CO-US-276-5866) In the demonstration, participants recruited from both sites will be provided with daily oral PrEP for 12 months with quarterly follow-up visits (questionnaires and clinical assessments). Participants are encouraged to adhere to daily regimen throughout the study. At enrollment, every participant will be given access to a WeChat-based PrEP education mini-app that has been pilot tested and refined in a previous study project among Chinese GBMSM [25]. Among the participants who successfully initiate PrEP through the study, the first 700 participants from both sites will be included in the stepped-wedge trial.

This stepped-wedge design will be a four-phased implementation organized into four clusters with each cluster starting the intervention at three-month intervals, so that by the end of the 12-month study period all clusters will receive the intervention. (Table 1) A pragmatic trial is aligned with the aim of our study as we are interested in examining the crowdsourced intervention in a real-world context rather than strictly measuring its efficacy in an ideal setting [26]. This stepped-wedge design allows the evaluation of the intervention’s external validity and informs public health decisions to promote PrEP adherence in at-risk populations [27].

**Table 1 Tab1:**
[figure not shown]
Stepped-wedge design of a crowdsourced intervention for facilitating PrEP adherence in at-risk populations in China

In this closed cohort stepped-wedge design, all participants will be identified at the onset of the trial. All participants will be engaged with the intervention or control condition at different crossover points. Minimal implementation lag will be expected as the predesigned interventions consist of social media components and immediately start and finish [22]. The control condition includes routine follow-up visits (surveys and clinical assessments) by community-based organizations and local hospitals following the setup of the demonstration study. The intervention condition includes a crowdsourced intervention to facilitate PrEP adherence.

### Eligibility

Eligibility criteria for participants in the intervention include: 1) 18 years old or older at the time of enrollment; 2) Chinese citizens, currently residing in Hubei or Guangdong province and planning to remain there for the next 12 months; 3) Having a smartphone with WeChat installed; 4) Must self-report at least one of the listed high-risk behaviors (a. Have sex with more than 1 partners in the past 90 days; b. Inconsistent condom usage in vaginal or anal sex in the past 6 months; c. Ongoing sexual relationships with an HIV-positive partner in the past 6 months; d. Participation in commercial sex work in the past 6 months; e. Any bacterial STI diagnosed or reported in the past 6 months); 5) No history of renal dysfunction; 6) No history of chronic hepatitis B (HBV) infection; 7) No HIV infection; 8) No indication for HIV post-exposure prophylaxis; 9) No signs or symptoms consistent with acute HIV infection.

Potential participants will be informed of this stepped-wedge trial when they initiate PrEP in the hospital by study volunteers. Signed informed consent will be required from all participants.

### Sample size

A total of 700 participants will be recruited from Hubei and Guangdong provinces. The sample size of this closed cohort, binary outcome, complete stepped-wedge RCT design was calculated using PASS Sample Size Software (NCSS LLC, Kaysville, Utah). The required sample size was calculated for the primary outcome. We assumed that a crowdsourced intervention will facilitate PrEP adherence among at-risk populations compared to the standard routine follow-up. This calculation was based on the Hussey and Hughes model postulating the cluster-specific departure from the average is homogeneous across time periods and intervention sequences [28, 29]. We assumed an intra-cluster correlation coefficient (ICC) of 0.02. Assuming an intervention effect of 0.2 (0.6 under intervention, 0.4 under control), a total of four clusters, four total intervention time periods. Two-sided Wald Z-Test alpha = 0.05, 80% power, the total sample size was 540. Accounting for 20% lost to follow-up, we increased the total sample size to 700 (175 for each cluster).

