Each follow-up at the 3, 6, 9, 12 months will include an online survey and a clinical assessment. (Table 1) The online survey will collect data related to number of sexual partners, HIV testing, PrEP uptake (missing doses in the past 90, 30, 7 days for daily PrEP users vs. number of sex and number of doses taken in the past 90, 30 days for on-demand PrEP users), engaging in WeChat mini-app, and evaluation of crowdsourced PrEP adherence intervention. Participants will be assessed on their PrEP attitudes, PrEP stigma, PrEP use self-efficacy, HIV-related anxiety, social support and overall perceived stress using validated scales at 6 and 12 months. For all follow-ups, transgender participants will additionally respond to questions related to whether they are currently using gender affirming hormones, and if they were, whether they are concerned about drug-drug interaction and whether they have mentioned taking hormones to the doctors who are prescribing PrEP. The clinical assessment will include testing results related to HIV, STIs (syphilis, HBV, HCV), standard blood test, standard urine test, liver function test, and renal function test. If a participant seroconverts to HIV positive, their participation in the study will be terminated and they will be referred to their local provider or health department for antiretroviral therapy. Otherwise, participants will be prescribed TDF-FTC for another 3 months after each follow-up at 3, 6, 9 months.

The primary outcomes of this sub-study are PrEP adherence and retention in PrEP care throughout the study period. PrEP adherence will be measured by self-report in quarterly behavioral assessment surveys and pill count at clinical follow-ups among a subset (a total of 120 participants who initiate PrEP during the study in Guangdong will be sampled to receive pill count using systematic random sampling). Retention in PrEP care will be measured via self-initiated or physician-advised PrEP discontinuation, PrEP re-initiation, and self-initiated switch rates from once daily and on-demand regimens. Details about the study measures are illustrated in Table 2. Optimal daily PrEP adherence will be considered to be 6–7 pills weekly. Optimal adherence to an on-demand regimen will be defined as having two pills at least 2 h before each sexual encounter, followed by one pill 24 hours after the first dose and one pill after the second dose.

**Table 2 Tab2:** Outcome measures and timepoints of data collection

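### The 540 given for 80% power does not reproduce as a number of participants; it matches a count of cluster-period observations, so the power statement does not describe this closed cohort

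*Protocol article*

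**What the plan says.** The Sample size section describes the method this way: "The sample size of this closed cohort, binary outcome, complete stepped-wedge RCT design was calculated using PASS Sample Size Software". On the model it says: "This calculation was based on the Hussey and Hughes model postulating the cluster-specific departure from the average is homogeneous across time periods". The inputs are "We assumed an intra-cluster correlation coefficient (ICC) of 0.02", "Assuming an intervention effect of 0.2 (0.6 under intervention, 0.4 under control") and "a total of four clusters, four total intervention time periods". The result is "Two-sided Wald Z-Test alpha = 0.05, 80% power, the total sample size was 540". The section then allows for 20% loss and arrives at 700, or 175 per cluster, so 540 is handled as a number of people.

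Under Study design and rationale the article says: "In this closed cohort stepped-wedge design, all participants will be identified at the onset of the trial". Under Study measures and outcomes it says: "Each follow-up at the 3, 6, 9, 12 months will include an online survey and a clinical assessment". Table 2 lists adherence at months 3, 6, 9 and 12, with no baseline value. The Timeline section adds a baseline survey. Each person therefore contributes up to four adherence assessments, and five surveys in all.

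**The concern.** The Hussey-Hughes formula works with the number of observations in each cluster-period. If a different group of people is measured in each period, total people equals the sum over all cells. In a closed cohort the same people fill every period, so the number of people is the number per cell times the number of clusters, and the sum over cells counts observations. A total over cells that is carried forward as people overstates the requirement by a factor equal to the number of periods.

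This is the article's only power statement, and it is the basis given for 700. If it does not describe the cohort being run, a reader cannot tell what size of effect the trial was built to detect, whether the result is null or a modest benefit.

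**Working it through.** **Inputs.** From Sample size: clusters I = 4; rates 0.6 and 0.4, so p(1-p) = 0.24 under both conditions; difference 0.20; ICC 0.02; two-sided Wald Z at 0.05; 80% power. Inferred: T = 5 periods (baseline plus months 3, 6, 9, 12), each cluster staying exposed once it starts. The article prints only the four intervention periods.

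**Formula.** With m observations per cluster-period, tau2 = 0.02 x 0.24 = 0.0048 and s2 = 0.2352/m:

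Var = I·s2·(s2 + T·tau2) / [(I·U - W)·s2 + (U² + I·T·U - T·W - I·V)·tau2]

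U is the number of exposed cells, W the sum of squared period totals and V the sum of squared cluster totals. Here U = 10, W = 30, V = 30. The denominator is 10·s2 + 30·tau2 for T = 5 and 10·s2 + 20·tau2 for T = 4. Power = Φ(0.20/SE - 1.96). The difference detectable with 80% power is 2.80 x SE.

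**Step 1: reproduce 540 (T = 5).**
- m = 27: s2 = 0.008711. Var = 4 x 0.008711 x 0.032711 / 0.231111 = 0.004932, SE = 0.0702, power 81.3%.
- m = 26: power 79.97%, just short.
- The smallest m is 27, and 27 x 4 x 5 = 540 exactly. Taking 0.24 as the within-cluster variance also gives 27 (80.5%).
- The match depends on inputs: a variance of 0.25 gives 28 per cell, or 560 observations.

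**Step 2: read 540 as people.** 540/4 = 135 per cluster in every period.

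| Case | SE | Power for 0.20 | Detectable difference |
|---|---|---|---|
| 135 per cluster, T = 5 | 0.0333 | 99.997% | 0.093 |
| 135 per cluster, T = 4 | 0.0359 | 99.985% | 0.100 |
| 140 per cluster, T = 4 | 0.0353 | 99.99% | 0.099 |

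The last row is 700 x 0.8 = 560 retained, at the four adherence assessments. With 135 per cell, power stays above 99.98% for every ICC from 0 to 0.99, so no choice of ICC makes 540 people correspond to 80% power. In the formula's own terms, 540 observations are 27 x 4 = 108 people measured five times. Other settings tried (four periods, other variance and ICC scales, one 3-month exposure per cluster) gave 64 to 148 people, and assumed positive within-person correlation gave fewer still. None gave 540.

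**Step 3: fit to the outcome schedule.** With T = 4 the smallest m is 29 (80.7%), or 30 on the other ICC scale. That is 29 x 16 = 464 or 30 x 16 = 480 observations, not 540.

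**Step 4: how far the detectable difference depends on the model** (140 per cluster, T = 4; every added input is an assumption).
- As stated: 0.099.
- Within-person correlation 0.3 to 0.7: about 0.084 to 0.056.
- Cluster autocorrelation 0.8 and 0.5: 0.12 and 0.14. At 0.5, power for 0.20 is about 98%.
- A t reference on 3 degrees of freedom in place of Z: 0.15. Combined with autocorrelation 0.5: about 0.21.
- Exposure coded as a single 3-month period per cluster: about 0.066.

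**The case against.** The article nowhere says that 540 counts observations, the software output is not shown, and the fifth period is not printed. A slightly different variance or number of periods breaks the exact match. This stands: the explanation is an inference. The mismatch does not depend on it, because no reading tried gave 540 people at 80% power.

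The error is also on the safe side. Under the stated model, at least 80% power for 0.20 is met with room to spare. It changes no allocation, endpoint or analysis, and results will carry 95% confidence intervals, which show directly what a null result excludes. Nor is 700 the bare inflated figure, since 540/0.8 = 675. All of this stands, and it limits the point to a reporting correction.

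Two stronger readings are tempting. A reader might infer that the trial is underpowered; under the stated model the arithmetic runs the other way. A reader might also infer that the trial really has more than 99.9% power, or can really detect 0.10. The documents do not support that either. Those figures assume permanent exposure, a cluster effect constant over time, and a large-sample test with four clusters. The plan describes a 3-month intervention per cluster and randomises blocks of eight. Step 4 of the working shows the answer moving from about half of 0.10 to about 0.21.

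**Conclusion.** The core holds. With the article's own inputs, 540 is not a number of participants that gives 80% power. It coincides exactly with 27 x 4 x 5 cluster-period observations, yet it is used as people in a cohort measured repeatedly. Read as people, the same model gives power above 99.9% for 0.20 and a detectable difference of about 0.09 to 0.10. That comparison rests on variance 0.24, ICC 0.02, a standard complete wedge, Wald Z and no within-person correlation. It shows that the stated size and stated power do not belong together; it does not estimate the trial's real power. A five-period calculation is a second, smaller mismatch, because adherence has four assessments. Should-fix: the consequence is a misleading power statement, not a loss of power under the stated model.

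**What to change.** - Confirm from the PASS output whether 540 is people or observations, and how many periods were entered.
- Restate the Sample size section with people per cluster, number of outcome periods and total observations.
- Rerun with a closed-cohort model for 560 retained of 700 (140 per cluster, four assessments). State the assumed within-person correlation and cluster autocorrelation, and use the actual randomised unit, a reference distribution suited to few clusters, and the exposure coding the analysis will use.
- Report power for 0.20 and the detectable difference as a range over those assumptions. Do not write in 99.9% or 0.10 as fixed figures.

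The cost is one rewritten paragraph and a rerun of the calculation. Enrolment does not change.

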### Intervention

The intervention consists of two parts: 1) intervention materials delivered to participants through WeChat in a stepped-wedge cluster randomized trial; 2) a series of judging by all participants on materials co-created by a small group of participants. The intervention effect will take into consideration of the two aspects. Intervention materials are developed through a nationwide open call in China.

### Intervention materials development – crowdsourcing open call

The intervention has been developed from a national crowdsourcing open call (Fig. 1). This crowdsourcing open call focused on identifying submissions to promote PrEP adherence among at-risk populations. Eligible submissions included concepts (< 1000 characters), images (photographs, posters, drawings), and multimedia contents (videos, audios, H5). All announcements related to the open call (promotions, deadlines, prizes) were channeled through social media platforms including WeChat and Weibo.

**Fig. 1 Fig1:**
[figure not shown]
Schematic of crowdsourcing intervention development and implementation

As of September 2021, the open call has received 19 submissions and each was evaluated by at least three independent judges. The judging panel consisted of CBO members, healthcare professionals and academics. Judges were selected based on their expertise in relevant sexual health topics and crowdsourcing. The quality of the entries was judged on relevance, feasibility, and elaboration. Judges received a full description of the judging criteria in advance and provided a single score on a 10-point scale. Following these judging criteria, all entries were screened to check for relevance to our open call and to identify plagiarism. People who submitted contributions that were determined to be in the top three were awarded cash prizes. Given that participation is important for crowdsourcing, the open call will keep running during the trial. This will allow participants to develop messages and ideas to iteratively enhance the intervention. The research team will also update the intervention by integrating selected materials from the ongoing open call every 3 months following the initial intervention (1.0). Materials will be adapted to formats compatible with the delivering platform WeChat.

Among the 19 submissions, eight were texts or slogans, two were videos, nine were posters, photos or comics. Five posters and one comic were selected by the judging panel as the most recognized contributions (see Supplement). The initial intervention (1.0) will integrate images from the six contributions. The themes of these images are focused on raising PrEP awareness by emphasizing the effectiveness and protective aspects of PrEP or on increasing PrEP knowledge in terms of who should take PrEP and the two types of PrEP medications. Core elements used in these images included posters, infographics, and comics.

The initial intervention (1.0) will integrate the recognized contributions for messages to encourage PrEP adherence. These materials will be combined with adjustments by the study team to allow for clear messaging. The intervention package will be channeled biweekly through WeChat and will allow for multiple deliveries during the intervention period. The intervention implementation will incorporate CBO peer educators or volunteers in Wuhan and Guangzhou as peer educators have access to the social media platform and are in close contact with the participants. CBO peer educators will be responsible for recruiting participants, following up with participants throughout the study period of 12 months, and implementing the intervention.

